### Statistical analysis plan

Descriptive analyses will estimate means and proportions, measures of variability, and confidence intervals of all measures. When defensible and part of the best available analysis strategy, observed distributions may prompt normalizing transformations. We will determine whether participant baseline characteristics are independent of intervention group assignment (randomization check) and attrition (attrition analysis). Case-wise deletion and other ad hoc approaches to handling missing data will not be used for analysis because they rely on relatively strong assumptions and entail a loss of statistical power. Instead, multiple imputation will allow models to be fit to all available data and will invoke the relatively mild assumption that the data are *missing at random*, conditional on modeled variables [60–63].

Primary analyses will include fitting regression models of continuous participant outcomes. The data has a 3-level structure (centers, participants, repeated measures), which will be accommodated with linear mixed models, including random intercepts both for centers and participants. The main study end-point will be the 6-month assessment. The modeled primary outcomes include the baseline and 6-month assessments of the primary physical, emotional, and cognitive variables (see Table 2). Each outcome will be regressed onto indicators of intervention group assignment and categorical time, as well as the group-by-time interaction. Significant intervention group main effects at 6-months and group-by-time interaction effects would be interpreted and described.

Secondary analyses include models of secondary outcomes that are conceptually similar to the models described above. We will also examine within-group comparisons of 6- and 12-month outcomes to determine any added benefits of extended choral activity and compare the effect of choral participation in the intervention group to that observed in the original control group after choral group participation is offered to them. We will also explore potential intervention effect moderators by fitting models that include key interaction terms; primarily, our focus will be on interactions between experimental group with participant sex, age, and race/ethnicity. The longitudinal models described above will be refit with the inclusion of 3-way interactions (e.g., experimental group-by-sex-by-time).

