#### Sample size calculations and power

We aimed to recruit 350 participants, approximately 30 from each of 12 senior centers. Assumptions included intention-to-treat analyses, 80 % power, two-tailed alpha = 0.05, 90 % retention at 6 months, unit-standardized continuous outcomes, and a linear mixed model of group differences at 6 months. Based upon published data from a study involving older adults who completed a year-long choir program [25], the largest intra-cluster correlation (ICC) for any outcome equaled 0.015. Accounting for ICC, cluster size, and attrition, the minimum detectable group difference, *d*, equaled 0.37, which compares favorably to effect sizes based upon the results reported by Cohen and colleagues [25]: overall health rating (0.41); depression (0.38); number of weekly activities (0.57 and 0.77).

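### The primary model lets baseline means differ by group, so neither of its two read-outs uses the baseline value as efficiently as a baseline-adjusted 6-month contrast would

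*Protocol article*

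**What the plan says.** The Statistical analysis plan section of the protocol article puts baseline on the outcome side: "The modeled primary outcomes include the baseline and 6-month assessments of the primary physical, emotional, and cognitive variables". The fixed effects are group, categorical time and their product: "Each outcome will be regressed onto indicators of intervention group assignment and categorical time, as well as the group-by-time interaction". The covariance comes from "linear mixed models, including random intercepts both for centers and participants". Two results are to be read: "Significant intervention group main effects at 6-months and group-by-time interaction effects would be interpreted and described". Neither is named as the treatment effect. The section does not enter the baseline value as a covariate or hold baseline means equal across groups.

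The Sample size calculations and power section sizes the trial on "a linear mixed model of group differences at 6 months" and mentions no correlation between baseline and follow-up.

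The Cluster randomization section says that assignment was disclosed only once recruitment in a pair of centers was finished. The Abstract places baseline assessment before assignment.

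**The concern.** Two groups at two times, with group, time and interaction all free, give four unconstrained cell means. With complete data, the 6-month contrast is then the raw difference at 6 months, and the interaction is the difference in mean change. The first makes no use of the baseline value. The second subtracts it in full, as if the regression of 6-month on baseline values had slope 1. When the correlation lies strictly between 0 and 1, the best use of baseline falls between these two.

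Power is one thing at stake. The other is what happens when the arms differ by chance at baseline. If the arm means of an outcome differ by δ at baseline, the 6-month contrast is expected to carry forward rδ, and the change contrast to over-correct by (1 − r)δ, where r is the correlation defined in the working. Because baseline was collected before allocation was known, equal expected baseline means follow from the design, and the model can use that fact.

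**Working it through.** **Inputs from the protocol article** (Sample size calculations and power): "We aimed to recruit 350 participants, approximately 30 from each of 12 senior centers"; "80 % power, two-tailed alpha = 0.05, 90 % retention at 6 months, unit-standardized continuous outcomes"; "the largest intra-cluster correlation (ICC) for any outcome equaled 0.015". Six centers per arm. The correlation ρ is assumed and varied from 0.3 to 0.9.

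**Step 1: reproduce the stated 0.37.**
- Analyzed n = 350 × 0.90 = 315; m = 315/12 = 26.25 per center.
- Design effect = 1 + 25.25 × 0.015 = 1.379.
- MDD = (1.960 + 0.842) × √(4 × 1.379/315) = 2.802 × 0.1323 = 0.371.
- Power at d = 0.37 is 79.9%.

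The stated figure is therefore right on its own inputs with normal quantiles, and it is the figure for an unadjusted 6-month comparison.

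**Step 2: variances under the stated model.** Take total variance 1, center variance τ = 0.015, participant variance ρ − τ, residual variance 1 − ρ, and m = 26 complete per center. For center means:
- variance at each time: A = τ + (1 − τ)/m = 0.015 + 0.985/26 = 0.0529;
- covariance between times: B = τ + (ρ − τ)/m;
- correlation: r = B/A.

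With six centers per arm:
- 6-month contrast: A/3 = 0.01763;
- interaction: (A/3) × 2(1 − r), which equals 2(1 − ρ)/(3m), because the center intercept cancels;
- common baseline mean: (A/3) × (1 − r²).

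Worked case, ρ = 0.6: B = 0.015 + 0.585/26 = 0.0375 and r = 0.0375/0.0529 = 0.709. The 6-month MDD is 2.802 × √0.01763 = 0.372. The interaction gives 0.372 × √0.582 = 0.284. The common baseline gives 0.372 × √0.497 = 0.262.

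| ρ (assumed) | r | MDD, 6-month | MDD, interaction | MDD, adjusted | Variance cut vs interaction, (1 − r)/2 | Variance cut vs 6-month, r² |
|---|---|---|---|---|---|---|
| 0.3 | 0.491 | 0.372 | 0.375 | 0.324 | 25% | 24% |
| 0.4 | 0.564 | 0.372 | 0.347 | 0.307 | 22% | 32% |
| 0.5 | 0.636 | 0.372 | 0.317 | 0.287 | 18% | 40% |
| 0.6 | 0.709 | 0.372 | 0.284 | 0.262 | 15% | 50% |
| 0.7 | 0.782 | 0.372 | 0.246 | 0.232 | 11% | 61% |
| 0.9 | 0.927 | 0.372 | 0.142 | 0.139 | 4% | 86% |

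At ρ = 0.5, power at d = 0.37 is 80% (6-month), 90% (interaction) and 95% (adjusted).

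**Step 3: sensitivity.**
- *Dropout.* With 29 per center at baseline and 26 at 6 months, the mixed model borrows a little from baseline. The 6-month MDD is then 0.371 at ρ = 0.3 and 0.361 at ρ = 0.9. At ρ = 0.5 the three MDDs are 0.369, 0.313 and 0.287. The pattern is unchanged.
- *Quantiles.* t quantiles with 10 df raise every MDD by about 11% and leave the ratios alone.
- *Form of adjustment.* The adjusted column is for a common baseline mean. With the baseline value as a covariate, the slope is close to the within-center value, (ρ − τ)/(1 − τ). At ρ = 0.6 this is 0.585/0.985 = 0.594, and the variance factor is 1 − 2(0.594)(0.709) + 0.594² = 0.51, against 0.50 in the table.

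**The case against.** The strongest reply is that this is a standard, valid analysis. Group, time and their interaction in a mixed model give unbiased contrasts under randomization, and refining the model could be left to an analysis plan that is not shown. The point on validity stands. But the article does not leave the model open: it sets out the fixed and random terms, and the efficiency loss follows from them.

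A second reply is that the loss against the interaction is modest. That also stands: it is 15% of variance at ρ = 0.6 and 4% at ρ = 0.9. The large loss is against the 6-month contrast, which is only one of the two read-outs.

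Three stronger readings are tempting, and the document does not support them.
- *That the change contrast is worse than the unadjusted one whenever ρ is below 0.5.* The person-level formula 2(1 − ρ) suggests this. In the stated model the center intercept cancels from the interaction, so the crossover is at r = 0.5. That requires B = 0.0264, so ρ = 0.015 + 26 × 0.0114 ≈ 0.31.
- *That the trial already fails to reach its stated detectable difference.* The 0.37 reproduces. A miss appears only if 10-df quantiles are substituted, which is a separate question.
- *That chance imbalance is likely.* The Cluster randomization section describes choosing among the best 23 of 462 partitions on the center characteristics in Table 1. These include age, race/ethnicity, income and functional impairment, so much of the difference between centers was addressed. The three primary outcomes are not in Table 1, however, so residual imbalance in them remains possible.

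**Conclusion.** The point holds as one of efficiency. Both planned read-outs are dominated by a baseline-adjusted 6-month contrast at every ρ strictly between 0 and 1. For ρ from 0.3 to 0.9, adjustment cuts variance by about 25% down to 4% against the interaction, and by 24% up to 86% against the 6-month contrast.

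The sizes depend on ρ, which is assumed. They also depend on the random-intercept structure as written, with no center-by-time variance, on ICC 0.015, and on variance components treated as known. The direction of the result does not depend on the value of ρ.

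The consequences are lost precision and avoidable sensitivity to residual baseline imbalance in the primary outcomes. Nothing here makes the planned tests biased or invalid, or the stated 0.37 wrong. Because the two read-outs have different variances and can disagree, leaving both open adds an ambiguity that the same change removes.

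**What to change.** Either drop the group term at baseline, so that the model has a common baseline mean, time, and a group effect at 6 months only; or model the 6-month outcome with the participant's own baseline value as a covariate. Keep the random center effects in both cases. Name the resulting 6-month group coefficient as the single primary treatment effect for each primary outcome.

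The cost is a few words in the analysis section. The baseline values are already part of the assessment schedule. The Discussion says that longitudinal data will not be examined until all sites have finished the 6-month randomized phase, so the change can be made before any comparative result is seen.

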## Method/design

### Overall study design

The Community of Voices study is a multi-site, cluster randomized trial, located in San Francisco, CA (study enrollment from February 2012 – August 2015). Twelve AoA- supported senior centers were randomized to receive the 12-month Community of Voices choir program immediately (intervention group) or after a 6-month delay (wait-list control group). Adults age 60 or older were recruited from the geographic service areas of each senior center. Recruitment and enrollment were conducted in staggered pairs of centers. We completed a comprehensive battery of outcome measures, including cognitive, physical, and psychosocial outcomes hypothesized to be mechanistically related to choral singing. We assessed primary and secondary outcomes for all participants at baseline, 6 and 12 months. Thus, for those in the control group, the study lasted 18 months (6 month wait period, 12- month choir). The main randomized comparison will be at 6 months. The 12-month assessment allows us to examine within-person change over the 12- month period of the choir.

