All primary and secondary outcomes were assessed at baseline, 6-months, and 12-months. For the convenience of participants, all assessments, including screening, took place at the senior center in which the person was enrolled. We collected data about falls and health care service utilization every three months either during the in-person assessments or by phone in between in-person assessments.

We used the National Institutes of Health (NIH) Assessment Center^SM^ as a platform to collect and manage all data (https://www.assessmentcenter.net). This is a free, secure, online data collection tool that provides real-time scoring of measures, automated accrual reports, and real-time data export. The Assessment Center enables researchers to create study-specific websites for capturing participant data securely online. Studies can include measures within the Assessment Center library such as the NIH Toolbox measures, as well as custom instruments entered by the researcher. We used the NIH Toolbox for the Assessment of Neurological and Behavioral Function [34] to assess many of the outcomes. The NIH Toolbox primarily uses a computer adapted testing (CAT) format based on item response theory (IRT); short-forms are also available which provide a fixed number of items. All NIH Toolbox measures are available in English and Spanish. We added several custom instruments that were not part of the Toolbox; all non-Toolbox measures were customized to be included as part of the Assessment center platform (e.g., format, randomization, skip patterns). All cognitive and physical function measures were performance based (e.g., required participants to perform a task such as walking or recalling words). All other measures were interviewer-administered. Below, we describe our primary and secondary outcomes including the rationale and specific measure used for each variable.

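### The benefit of longer choir participation rests on an uncontrolled 6-to-12-month change, while the listed month-12 visits already give a randomized comparison that the stated plan does not use

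*Protocol article*

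**What the plan says.** Under Overall study design, centers are randomized to a 12-month choir that starts at once or after six months. "We assessed primary and secondary outcomes for all participants at baseline, 6 and 12 months", and "The main randomized comparison will be at 6 months". The same section says that "for those in the control group, the study lasted 18 months", made up of the wait and then a full year of choir. It adds: "The 12-month assessment allows us to examine within-person change over the 12- month period of the choir".

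Study outcomes and data collection methods repeats the schedule: "All primary and secondary outcomes were assessed at baseline, 6-months, and 12-months".

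Under Statistical analysis plan, the primary mixed model holds the baseline and 6-month assessments only. The secondary analyses include "within-group comparisons of 6- and 12-month outcomes to determine any added benefits of extended choral activity". The same sentence goes on to a second analysis, which compares the choir effect in the intervention arm with the choir effect seen in former controls once they are offered the choir.

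**The concern.** A change from month 6 to month 12 within one arm cannot separate continued choir from whatever else happens over those six months. On a timed task such as Trail Making, a third administration may bring practice gains. Ageing may pull performance the other way. The verb *determine* promises an attribution that such a change cannot carry: drift towards improvement would be credited to the choir, and drift towards decline would hide a real benefit.

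The wording also does not name an arm, and the period means different things in the two arms. Meanwhile the month-12 visit, if held as listed, gives a comparison of randomized arms after equal follow-up and equal numbers of tests. The stated plan leaves that comparison out.

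**Working it through.** **Exposure grid from the stated schedule (months of choir received)**

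| Study month | Immediate start | Wait-list |
|---|---|---|
| 0 | 0 | 0 |
| 6 | 6 | 0 |
| 12 | 12 | 6 |
| 18 (no outcome visit listed) | finished | 12 |

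The 6-to-12-month change is extended choir in the immediate arm and first exposure in the wait-list arm. At month 12 the randomized arms stand at 12 against 6. At month 18 the wait-list arm completes its year, but no outcome visit is listed there.

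**The plan's own figure.** Inputs from Sample size calculations and power: 350 participants, 12 centers, ICC 0.015, 90% retention at 6 months, 80% power, two-sided alpha 0.05.
- n = 350 × 0.90 = 315; m = 315/12 = 26.25
- Design effect = 1 + (26.25 − 1) × 0.015 = 1.379
- SE = sqrt(4 × 1.379/315) = 0.132
- Minimum detectable d = (1.960 + 0.842) × 0.132 = 0.371

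The stated 0.37 is reproduced.

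**The same formula at month 12.** Retention at month 12 is not given, so it is varied as an assumption:

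| Assumed retention | Minimum detectable d, unadjusted, normal reference |
|---|---|
| 90% | 0.371 |
| 85% | 0.378 |
| 80% | 0.387 |
| 70% | 0.407 |

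With a t reference on 10 df (12 centers minus 2) the range is about 0.41 to 0.45. Baseline adjustment would help. If the baseline-to-month-12 correlation is 0.6, the SE is multiplied by sqrt(1 − 0.36) = 0.8, and 0.371 becomes about 0.30.

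**What drift does to the within-arm change (illustration).** Assumptions: 157.5 analyzed in the immediate arm (half of 315), correlation 0.6 between months 6 and 12, true added benefit zero.
- No design effect: SE = sqrt(2 × 0.4/157.5) = 0.071
- With design effect 1.379: SE = sqrt(2 × 0.4 × 1.379/157.5) = 0.084
- Probability of a significant result in the drift direction = Φ(drift/SE − 1.96)

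| Drift | With design effect | Without |
|---|---|---|
| 0.10 SD | 22% | 29% |
| 0.15 SD | 43% | 56% |
| 0.20 SD | 67% | 80% |

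The column without a design effect is closer to the stated model, because a random center intercept shared by both visits cancels in a within-person change. Letting the correlation run from 0.5 to 0.8, without clustering, gives 24% to 51% at 0.10 SD and 71% to 98% at 0.20 SD. Drift common to both arms cancels in expectation in the month-12 between-arm difference.

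**Precision given up.** On the same assumptions the within-arm change has a minimum detectable value of 2.802 × 0.071 = 0.20 or 2.802 × 0.084 = 0.23 SD, against about 0.37 SD for the unadjusted between-arm contrast.

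**The case against.** The strongest reply is that this is a secondary analysis, openly described as within-person, and that neither the primary comparison nor the sample size depends on it. That stands and limits the weight of the point.

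The sentence also has a second half, which gives former controls their own comparison. It is natural to read the first half as meant for the immediate arm. That reading is fair and the fix adopts it. But the second half sets choir effects from different study periods side by side. It asks whether the effect recurs in former controls, not whether 12 months adds to 6.

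Some stronger readings are tempting and are not supported:
- *The arms at month 12 differ only in length of choir.* They also differ in start time, in having waited six months, in how recent the first phase is, and possibly in dropout. The contrast is immediate versus delayed start. It is randomized, but it is not a pure dose comparison, and it is a different estimand from continued benefit in the same people.
- *The within-arm change will overstate the choir.* The direction is not known. Practice is a plausible upward drift for Trail Making, but no such case is made for PHQ-8 or chair stands, and ageing would tend to mask benefit. Staggered paired recruitment should spread season at least partly, and multiple imputation with an attrition analysis lessens the dropout concern.
- *The false-positive rates are properties of this trial.* They follow from assumed drift and correlation.
- *No month-12 contrast is planned anywhere.* This is a condensed article and the full analysis plan is not shown. What can be said is that the text gives this question to the within-group comparison and states no between-arm one.

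On the schedule, the 12-month assessment might be counted from choir start in the wait-list arm. In that case a later visit exists and is simply not listed. The text would still need correcting. The main point would also stand, provided controls were assessed after six months of choir, which is study month 12.

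**Conclusion.** The point holds as a worthwhile improvement to a secondary analysis. An uncontrolled 6-to-12-month change cannot determine added benefit, and the listed visits already supply a randomized contrast that bears on the question better. The false-positive figures (roughly 22-29% at 0.10 SD to 67-80% at 0.20 SD of drift, r = 0.6) are illustrative only. The month-12 contrast has a minimum detectable difference of about 0.37 to 0.41 SD, assuming 90% to 70% retention and a normal reference, so it may well miss a modest increment.

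The schedule mismatch is real but small. Controls are said to take part for 18 months, and the 12-month assessment is said to cover the year of choir, yet no outcome visit after month 12 is listed. None of the analyses described requires a later visit, so this is a matter of reconciling the text.

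**What to change.** 1. Add the between-arm difference at month 12, adjusted for baseline and center clustering, as the inferential analysis of extended participation. State that it compares immediate with delayed start and is not a pure dose contrast.
2. Keep the 6-to-12-month change in the immediate-start arm, label it descriptive, and replace *determine* with wording that makes no attribution.
3. State beforehand that a non-significant month-12 difference is not evidence of no added benefit, and report the interval.
4. Reconcile Overall study design with Study outcomes and data collection methods: either list the later visit for wait-list centers, or limit the statement about the 12-month choir period to the immediate-start arm.

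On the listed schedule this needs no new data, only wording and one added contrast. The price is the lower precision shown above. The Discussion says that longitudinal data will not be examined until all sites finish the 6-month randomized phase. While that holds, the contrast can be fixed before anyone has seen results.

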The overall music style (e.g., Latin folk music, show tunes, traditional African American music, and Filipino folk music) for each choir was selected by the music center after meeting with each senior center director and considering the cultural backgrounds and music preferences of the older adults they served. The repertoire was further refined in terms of cultural relevance and complexity during the first several weeks after the start of each choir, and requests for specific songs were considered. The repertoire was selected to be appropriate for older adults with a range of singing abilities and prior experience with choral singing (from beginner to advanced levels).

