### Measures of fidelity and compliance to choir intervention

The fidelity of the Community of Voices program across senior center sites, choir conductors, and styles of music was tracked using a 16-item survey with a 4-point scale. The fidelity survey focused on (i) implementation of the three key components of the choir program (cognitive, physical, and psychosocial engagement), (ii) leadership/communication skills, and (iii) musicianship. For each item, a score of 4 indicated that the performance of the conductor/accompanist exceeded program expectations; 3 indicated that the item met program expectations, 2 indicated that it was below expectations, and 1 indicated that it was not addressed and was well below expectations. The PI completed the fidelity check every three months, with an additional assessment three weeks after each choir began. Feedback was provided to conductors if the fidelity ratings on any of the 16 items fell below 3.

To assess compliance to the intervention, attendance was recorded at each choir session by the choir directors, and research staff coded absences according to the reason for the absence (e.g., illness, medical appointment, vacation, family issues).

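### The exploratory race/ethnicity moderator term cannot separate a participant's ethnicity from the choir received, because choir style is matched to each center's culture

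*Protocol article*

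**What the plan says.** The Statistical analysis plan section of the protocol article introduces moderators among the secondary analyses: "We will also explore potential intervention effect moderators by fitting models that include key interaction terms". Three moderators are named: "our focus will be on interactions between experimental group with participant sex, age, and race/ethnicity". The model is also fixed: "The longitudinal models described above will be refit with the inclusion of 3-way interactions". The models to be refit are linear mixed models "including random intercepts both for centers and participants". No term lets the 6-month change differ by center, and none separates a participant's ethnicity from the ethnic make-up of the center.

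The section on the choir program says that the overall music style "for each choir was selected by the music center after meeting with each senior center director and considering the cultural backgrounds and music preferences". The people meant are those whom the center serves. Its examples include Latin folk, traditional African American and Filipino folk music. Tailoring continued after the start: "The repertoire was further refined in terms of cultural relevance and complexity during the first several weeks after the start of each choir". The fidelity section describes tracking the program "across senior center sites, choir conductors, and styles of music", so conductors and styles both varied by site.

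**The concern.** Center ethnic mix and choir content are linked by design, and only six choirs are running in the 6-month randomized comparison. A group-by-ethnicity-by-time coefficient on the raw participant variable averages two contrasts:

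- within a center: participants of different ethnicity who are offered the same choir;
- between centers: participants offered different choirs, with different music and conductors.

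Only the first holds the choir fixed. If one or two choirs work better for everyone in them, and those centers mostly serve one ethnic group, the coefficient is non-zero although participant ethnicity changes nothing. In a trial motivated by diversity and health disparities, a significant term would naturally be read as the choir working better or worse for an ethnic group, when the cause could be a style or a conductor.

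**Working it through.** **The plan's own figure.** From the sample size section: 350 participants, 12 centers, 90% retention, ICC 0.015, two-sided alpha 0.05, power 80%.

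- n per arm = 350 × 0.9 / 2 = 157.5; retained cluster size = 350 × 0.9 / 12 = 26.25.
- Design effect = 1 + (26.25 − 1) × 0.015 = 1.379.
- d = (1.960 + 0.842) × √(2 × 1.379 / 157.5) = 0.371.

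The stated 0.37 reproduces. It concerns the main effect; no figure is given for the moderator test.

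**Reduction to change scores.** With baseline and 6 months only, the random intercepts cancel, and the three-way term equals the group-by-ethnicity term in a regression of change. In three simulated data sets fitted both ways, the estimates were identical and the standard errors agreed to within 0.00001.

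**Assumptions (not in the document).** Two ethnic groups; two of six centers per arm with a style matched to one group; the same mix in both arms; 26 analysed per center (156 per arm); outcomes in SD units; baseline-to-6-month correlation r. A split of 85/5 means that the group makes up 85% of its matched centers and 5% of the others. The matched style adds s SD for everyone in that choir, so true modification by participant ethnicity is zero.

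**Spurious interaction.** It equals s × [P(matched center | in group) − P(matched center | not in group)].

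- 85/5: 1.70/1.90 − 0.30/4.10 = 0.895 − 0.073 = 0.822
- 70/15: 1.40/2.00 − 0.60/4.00 = 0.550
- 60/20: 1.20/2.00 − 0.80/4.00 = 0.400

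For s = 0.37 the bias is 0.30, 0.20 and 0.15 SD; for s = 0.2 it is 0.16, 0.11 and 0.08 SD.

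**False-positive rate.** SE = √[2(1 − r) × 2 / (156 V)], where V = p(1 − p) and p is the group's overall share. V is 0.216 at 85/5 and 0.222 at the other two splits. Worked case, 85/5, r = 0.5, s = 0.37: SE = √[2 / (156 × 0.2164)] = 0.243; bias/SE = 0.304/0.243 = 1.25; P(Z > 1.96 − 1.25) is about 24%.

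| Split | s = 0.2, r 0.5 / 0.7 | s = 0.37, r 0.5 / 0.7 | Simulated, s = 0.37 (2,000 trials) |
|---|---|---|---|
| 85/5 | 10% / 14% | 24% / 36% | 23.8% / 37.4% |
| 70/15 | 7% / 9% | 13% / 19% | 14.0% / 18.8% |
| 60/20 | 6% / 7% | 9% / 12% | 9.0% / 11.8% |

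Without choir differences the raw term rejected 4.6-5.8% of the time. The within-center term stayed at about 5%, with bias near zero. With ethnicity spread evenly over centers there was no inflation.

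**A milder benchmark.** An ICC of 0.015 corresponds to a between-center SD of √0.015 = 0.12. With choir effects varying at random by that much, unrelated to style, 4,000 simulated trials at r = 0.5/0.7/0.8 gave 5.9/8.1/8.6% at 85/5, 5.6/5.9/7.6% at 70/15, and about 5-6% at 60/20.

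**Does a center-by-time random effect suffice?** At 85/5 and s = 0.37, a refit with that term still gave a mean spurious interaction of 0.29 (r = 0.5) and 0.26 (r = 0.7), rejecting 17.3% and 22.5%. This rests on about 290 fits per setting, some with convergence warnings, so it is only indicative. The random effect corrects variance; it does not separate the two contrasts.

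**The case against.** The best counter-argument concerns the question being asked. The abstract calls the program culturally tailored, so matched music is part of the intervention. Whether the program as delivered benefits ethnic groups differently is a legitimate question, and the overall interaction addresses it. Nor is the within-center term free of style: in a style-matched choir it compares matched with unmatched members. This stands. A reader might infer that the planned term is invalid, or that the within-center term is the only permissible one; the documents support neither. They support only that the overall term should not by itself be attributed to participant ethnicity.

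The size is also assumed. The article gives neither ethnic mix by center nor the spread of choir effects, and 0.37 SD for style alone equals the whole detectable treatment effect. Against the stated ICC, which itself comes from one earlier study and describes outcomes rather than choir effects, inflation is slight. This stands too. A scenario with large random choir effects (SD 0.3, rejecting 14-25% at 85/5) should not be counted as bias: its mean error is zero and its inflation comes from the missing center-by-time term.

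The program components were standardized in a manual, fidelity was scored, and a choir can be multi-cultural. These soften the concern, but style, repertoire and conductor still varied. That choirs can be mixed is what makes a within-center contrast estimable.

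Finally, such detail is often left to a fuller plan. Here, though, the article states the model itself.

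**Conclusion.** The point holds as a limit on what the race/ethnicity term can show. As specified, it cannot distinguish modification by participant ethnicity from differences between choirs. Harm requires both clustering of ethnicity by center and choir effects that differ. Under the assumed splits and r of 0.5 to 0.7, false positives are about 6-14% for a 0.2 SD style effect and 9-37% for 0.37 SD. Under the ICC-based benchmark, with r up to 0.8, they are about 5-9%. These are illustrations, not estimates for this trial.

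The importance is moderate: the analysis is exploratory, and neither the 6-month primary comparison nor the detectable difference of 0.37 is touched. A reader might extend the point to sex and age, which share the same model, but nothing in the document ties choir style to either.

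**What to change.** In the Statistical analysis plan section, for race/ethnicity only:

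1. Split each race/ethnicity indicator into the participant's deviation from the center mean and the center mean.
2. Enter both parts with group and time in the three-way model, and include a center-by-time random effect.
3. Report both terms beside the overall interaction. Describe the overall and between-center terms as the program-as-delivered contrast, confounded with choir style and conductor.
4. Attribute moderation to participant ethnicity only where the within-center term supports it.

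No new data are needed. The cost is precision. The within-center standard error grows by about √(V/W), where W is the average within-center variance of ethnicity: √(0.222/0.187) = 1.1 at 60/20, √(0.222/0.155) = 1.2 at 70/15, and √(0.216/0.074) = 1.7 at 85/5 (1.8 in simulation). Where centers are nearly homogeneous, the term rests on the few atypical members of each center. The between-center term rests on six choirs and will also be imprecise.
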